### Plans to promote participant retention and complete follow-up {18b}

Data collection and recording will be carried out by specific research study staff to ensure data integrity. Some data will also be checked using the memory of patients’ monitors.

### Data management {19}

Data will be collected on a Case Record Form (CRF) table and managed on the ResMan clinical trial public management platform (http://www.medresman.org.cn). Two investigators will be responsible for data entry and verification in each enrolling hospital. Research progress will be checked regularly.

## Statistical methods

### Statistical methods for primary and secondary outcomes {20a}

Data processing will be performed by the statistician in our research group and analyzed under an intention-to-treat premise. A two-tailed p-value less than 0.05 will be defined as statistically significant.

#### Description of patients’ basic characteristics

Measurement data will be described using means and standard deviations or median and inter-quartile range based on the data distribution characteristics. Calculated data is displayed as a frequency or a percentage.

#### Analysis of the primary outcome

The lowest SpO_2_ values of each subject will be imported to the SPSS software. Then, the normal distribution test and homogeneity test of variance will be performed. Finally, according to the results, the lowest SpO_2_ will be compared by the independent sample T-test or rank-sum test.

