## Methods: participants, interventions, and outcomes

### Study setting {9}

This study will be led by the Emergency Department of Peking Union Medical College Hospital in Beijing, China. Three other hospitals will also enroll patients, including the First Affiliated Hospital of Xinjiang Medical University in the Xinjiang Uygur Autonomous Region, the Second People’s Hospital of Huai’an, and the Suqian People’s Hospital in Jiangsu province in China. These are all grade III A hospitals with adequate medical consultants, qualified doctors, and monitoring equipment to fulfill this study.

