### Outcomes {12}

#### Primary outcome measure

The primary outcome measure is the lowest oxygen saturation recorded via pulse oxygen saturation monitoring during the intubation procedure. The intubation procedure starts when the laryngoscope blade is inserted and ends once the endotracheal tube position is confirmed. Since there may be further delays of the pulse oxygen saturation, data will continue to be recorded until 2 min after intubation ends.

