### Sample size {14}

According to published studies, the mean oxygen saturation in control groups during intubation has been found to be 88% [21]. We posit that the intervention group may be increased by 5% and that the standard deviation will be 12%. Using a two-tailed α = 0.05, and β = 0.20, the sample size of the intervention group and control group were calculated using PASS 11 software to be N1 = N2 = 72 cases, or 144 cases total.

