## Assignment of interventions: allocation

### Sequence generation {16a}

SPSS software will be used to generate the corresponding number of random sequences according to the sample size. And then, the random values will be divided equally into two groups as the control group and the intervention group. Patients involved in this research will be randomly assigned to these two groups. The grouping arrangement will not be changed once the research project is underway.

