## Data collection and management

### Plans for assessment and collection of outcomes {18a}

Before randomization, some basic information will be recorded: patient identification number, age, sex, height, weight, body mass index, primary diagnosis, reason for intubation, systolic blood pressure, vasopressor use before intubation including the type and dosage, and any oxygen therapies used, including FiO_2_ and duration of use, pulse oximetry (SpO_2_) before intubation, and recent blood gas analysis (pH, PaO_2_, arterial carbon dioxide partial pressure (PaCO_2_)); any history of a difficult airway, airway evaluation using the MACOCHA score, and the time since the patient’s last meal will be recorded.

According to this basic information, patients who meet eligibility criteria will be randomized. A member of the research staff will select the corresponding BVM device for use prior to intubation. During the procedure, another member of the research staff will record key data. For example, the induction medicine (including drug name and dosage), the duration of BVM ventilation, the SpO_2_ before inserting the laryngoscope, the duration between inserting the laryngoscope and 2 min after intubation, the number of intubation attempts, the lowest SpO_2_ during the procedure, the lowest systolic blood pressure, any vasopressor use, and any incidence of aspiration or cardiac arrest.

During prophylactic BVM ventilation, some additional parameters will be monitored. Data such as exhaled tidal volume, respiratory rate, exhaled oxygen concentration, and partial pressure of end-tidal carbon dioxide will be collected to guarantee consistent manipulation and avoid bias caused by improper operation.

Intubation will be performed by physicians with at least 3 years of previous intubation experience to ensure patient safety. All data will be recorded in the Case Record Form and managed by the ResMan clinical trial public management platform. After collection, data will be analyzed by the statistician in our research group.

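### Pretests choose the primary test; on the protocol's own planning figures they lead to the rank-sum test, so the 5-point mean difference used for sizing is neither tested nor estimated, and baseline SpO2 goes unused

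*Protocol article*

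**What the plan says.** Under Primary outcome measure: "The primary outcome measure is the lowest oxygen saturation recorded via pulse oxygen saturation monitoring during the intubation procedure".

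Under Analysis of the primary outcome, the values go into SPSS, "the normal distribution test and homogeneity test of variance will be performed", and the groups then "will be compared by the independent sample T-test or rank-sum test", depending on what the pretests show. Both candidates are unadjusted two-group tests.

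Sample size {14} works in means. It takes a control mean of 88% and continues: "We posit that the intervention group may be increased by 5% and that the standard deviation will be 12" (percent). With two-tailed α = 0.05 and β = 0.20 it arrives at 72 per arm.

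Plans for assessment and collection of outcomes {18a} begins: "Before randomization, some basic information will be recorded". SpO2 before intubation is on that list. The same section also records, later and during the procedure, the SpO2 just before the laryngoscope is inserted.

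**The concern.** Pulse oximetry cannot exceed 100%, and the planned means lie close to that ceiling relative to an SD of 12. A normality test on such data has a foreseeable result. The protocol therefore appears to offer two tests while its own assumptions leave only one in play, and that one does not address the quantity used for sizing. A rank-sum test compares the ordering of values between arms. It does not estimate a difference in means.

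At stake is what the trial will be able to report: a mean difference in SpO2 points with an interval, comparable with the planned 5 points, or a p-value about ranks. A reader cannot tell which from the protocol, because the choice is formally left to the outcome data.

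The second part concerns information already collected. In patients intubated for acute respiratory failure, SpO2 before randomisation can be expected to carry information about the lowest SpO2. Neither named test can use it.

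**Working it through.** **Inputs.** Sample size {14}: means 88 and 93, SD 12, two-tailed α 0.05, power 80%, 72 per arm. The cap of 100 is a property of the measure. The baseline correlation ρ is an assumption; the protocol gives none.

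**1. The plan's own figure.** n per arm = 2(z₁₋α/₂ + z₁₋β)² SD²/δ² = 2 × (1.960 + 0.842)² × 144/25 ≈ 90.4, so 91. The stated 72 is not reproduced. A one-sided α of 0.05 gives 2 × (1.645 + 0.842)² × 144/25 ≈ 71.2, so 72. That is a separate problem with the sample size. Here it only sets the reference: at 72 per arm, SE = 12 × √(2/72) = 2.0, 5/2.0 = 2.5, and two-sided power is Φ(2.5 − 1.96) = 0.705, or 0.700 by the t distribution.

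**2. Can the data be normal?** Let b = (100 − mean)/SD.

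| Arm | b | Normal tail above 100% | Upper bound on skewness, b − 1/b |
|---|---|---|---|
| Control | 12/12 = 1.00 | 15.9% | 0 |
| Intervention | 7/12 = 0.58 | 28.0% | −1.13 |

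The last column is the largest skewness that a variable capped at 100 can have with that mean and SD. The intervention arm must be strongly left-skewed. The control arm cannot be right-skewed, and 15.9% of a normal curve with its mean and SD would lie above the cap.

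**3. Does the pretest detect it at 72 per arm?** Simulation: 1,500 trials in each of five shapes capped at 100 (three scaled betas, a censored normal, 100 minus a gamma), each with means 88 and 93 and SD 12, rounded to integer SpO2, all tests at 0.05.

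- Shapiro-Wilk rejected in 100% of trials in each arm, in every shape.
- Lilliefors rejected in 98.6–100% (control) and 100% (intervention); at least one arm was rejected in 100% of trials.
- Type I error of the two-stage rule: 5.1–5.7%.
- Power: t-test 69–72%, rank-sum 93–99.6%.

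**4. Does the choice of quantity matter?** In the same five shapes the mean difference is 5 throughout, while the difference in medians runs from 97.9 − 91.7 = 6.2 to 100.0 − 90.6 = 9.4 points. Near a ceiling, one location measure does not stand in for another.

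**5. Gain from baseline adjustment over the unadjusted mean comparison.** Residual SD = 12√(1 − ρ²), 72 per arm, difference 5, two-sided 0.05, t-based power:

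| Assumed ρ | Residual SD | Power |
|---|---|---|
| 0 | 12.00 | 70.0% |
| 0.3 | 11.45 | 74.0% |
| 0.4 | 11.00 | 77.3% |
| 0.5 | 10.39 | 81.8% |
| 0.6 | 9.60 | 87.4% |

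A correlation of about 0.47 is needed for 80%. These are normal-theory figures.

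**6. The linear model against the rank-sum test.** In simulations of two capped shapes, the linear model had 72–81% power at assumed correlations of 0.3–0.5, and the rank-sum test about 99%.

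**The case against.** The strongest reply is that if the pretest always fails, the test is in effect fixed: it is the rank-sum test, which is valid and in these shapes more powerful. Much of this stands.

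- *Type I error.* A reader might infer that choosing the test from the data inflates the false-positive rate. The simulated 5.1–5.7% shows no material inflation.
- *Power.* A reader might infer that adjustment restores power the trial would otherwise lose. That holds only against the unadjusted t-test, which would hardly ever be run. Against the rank-sum test the mean-based model is clearly weaker in several ceiling-skewed shapes. The direction depends on shape: in another set of three capped shapes rank-sum power ranged from 67% to 99%, against 67–73% for the t-test.
- *Hypothesis.* The protocol's stated hypothesis is higher saturation and less hypoxia. The 5 points appear only in the sizing assumption, so the mismatch is between the test and the sizing basis.
- *Hospitals.* The protocol says "Three other hospitals will also enroll patients" and that "the random values will be divided equally into two groups as the control group and the intervention group". A reader might infer that hospital imbalance biases the comparison and that the list should be redone in blocks by hospital. The documents do not support this. They give no between-hospital variance and no site sizes, enrolment has already begun, and Sequence generation {16a} rules out changing the grouping once the project is underway.
- *Left to the SAP.* Covariates often are, and an unadjusted comparison is valid under randomisation. But this protocol does not leave the matter open: it names the pretests and two unadjusted tests.

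What the reply does not answer is that the trial was sized on a difference in means and is set to report a comparison of ranks.

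**Conclusion.** The concern holds in limited form. On the protocol's planning figures, normality would in practice always be rejected, the rank-sum test would be the primary analysis, and the planned 5-point mean difference would be neither tested nor estimated. Pre-randomisation SpO2 is collected but unused. Using it would raise power for the mean comparison from 70% to about 74% at an assumed correlation of 0.3 and 82% at 0.5.

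The pretest result is conditional on means of 88 and 93 with SD 12; lower means or a smaller SD would weaken it. The gain from adjustment rests wholly on the assumed correlation. The case for change is a fixed, interpretable estimand and use of baseline data. It is not error control, power over the rank-sum test, or hospital imbalance. The change should be made, but the validity of the trial does not depend on it.

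**What to change.** Drop the normality and variance pretests. Before unblinding, prespecify one primary analysis: a linear model of lowest SpO2 on arm and pre-randomisation SpO2, with robust standard errors, reporting the adjusted mean difference and its 95% CI. The covariate must be the value recorded before randomisation. The reading taken before laryngoscope insertion follows the allocated ventilation, and adjusting for it would remove part of the effect under study. Keep the rank-sum test, or a baseline-adjusted rank analysis, as a named sensitivity analysis. A hospital term is optional.

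The cost is a few sentences and a routine model on data already collected, with no extra patients and no change to the randomisation. The downside should be stated in the plan: with strong ceiling skew the rank-based test may well be the more powerful of the two, so the primary and sensitivity analyses may disagree, and the plan should say that the primary result is the mean difference.

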#### Analysis of secondary outcomes

The frequency and incidence rate of relevant complications, including SpO_2_ less than 80%, aspiration, systolic arterial blood pressure less than 90 mmHg, cardiac arrest, will be calculated in both groups. Then, based on the number of complications, select the chi-square test or Fisher’s exact probability test for comparison.

### Methods for additional analyses (e.g., subgroup analyses) {20b}

No subgroup analyses will be performed.

### Methods in analysis to handle protocol non-adherence and any statistical methods to handle missing data {20c}

This study adopts an intention-to-treat strategy to conduct data analysis. Subjects will be excluded if significant outcome data is missing.

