#### Dropout criteria

Patients enrolled in this study quit for whatever reason before the ending or their data miss too much to analyze. Either situation could drop out the subjects.

Before the study, investigators will be trained to gather information timely and thoroughly explain the research process and related details to lower the possible dropouts.

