### Criteria for discontinuing or modifying allocated interventions {11b}

Patients could opt out of the study at any time. If hypotension, reflux aspiration, or other possible adverse reactions occur during BVM ventilation, we will stop and take corresponding measures to treat any adverse reactions.

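### Intention-to-treat is declared, but the stated missing-data and dropout rules allow randomised patients to be removed without a threshold, which makes the analysis complete-case at subject level

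*Protocol article*

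**What the plan says.** Under Statistical methods {20a}, the data are to be "analyzed under an intention-to-treat premise". Section {20c}, on non-adherence and missing data, repeats it: "This study adopts an intention-to-treat strategy to conduct data analysis". The next sentence of {20c} reads: "Subjects will be excluded if significant outcome data is missing".

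The Dropout criteria describe two situations: "Patients enrolled in this study quit for whatever reason before the ending or their data miss too much to analyze". The consequence given is: "Either situation could drop out the subjects".

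Section {11b} lets patients opt out at any time and adds: "If hypotension, reflux aspiration, or other possible adverse reactions occur during BVM ventilation, we will stop and take corresponding measures". It does not say whether such a patient stays in the study or in the analysis.

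Section {18b} says: "Some data will also be checked using the memory of" the patients' monitors. Under Outcomes {12}, the primary outcome is the lowest SpO2 from insertion of the laryngoscope blade to confirmation of tube position, with recording continued for a further 2 minutes.

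**The concern.** Intention-to-treat means that every randomised patient is analysed in the assigned arm. A rule that takes out randomised patients after the event, because an outcome is missing or because they quit, is a different analysis. Three features make this more than loose terminology.

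- **No threshold.** Nothing defines how much missing data is too much or which outcome data count as significant, and nothing requires the decision to be made blind to arm.
- **Whole subjects are removed, not single values.** Read literally, a patient with no recorded lowest SpO2 also leaves the counts of aspiration, low systolic pressure and cardiac arrest in {20a}. Sections {21b} and {22} base early termination on a statistically higher incidence of complications, so the harm check could lose patients who had events.
- **Missingness could be related to outcome.** A patient whose ventilation is stopped for an adverse reaction under {11b}, or who opts out, may be more likely to have incomplete data. No section says that such patients are kept in.

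At stake is the protection that randomisation gives to the primary comparison, and the completeness of the safety counts.

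**Working it through.** **1. The passages side by side**

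| Place | What it fixes | Compatible with analysing all randomised patients? |
|---|---|---|
| {20a}, {20c} first sentence | intention-to-treat | yes |
| {20c} second sentence | subject excluded if significant outcome data are missing | no |
| Dropout criteria | subject could be dropped for quitting or for too much missing data | no, where applied |
| {11b} | ventilation stopped for an adverse reaction | silent on analysis status |

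The contradiction lies within the current text and needs no arithmetic.

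**2. The plan's own figure, and the room it leaves for exclusions**

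Inputs from Sample size {14}: control mean 88%, difference 5 points, SD 12, two-tailed α = 0.05, β = 0.20, 72 per arm.

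n per arm = 2(z_α + z_β)² × SD² / difference²

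- Two-sided: 2 × (1.960 + 0.842)² × 144/25 ≈ 90.4, so 91.
- One-sided 0.05: 2 × (1.645 + 0.842)² × 144/25 ≈ 71.2, so 72.

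The stated 72 therefore matches only a one-sided calculation. That is a separate point. What matters here is that the number carries no stated allowance for exclusions. Two-sided power at 72 per arm is 70.5%. If 5% or 10% of each arm were excluded (assumed rates), it would be 68.3% or 66.0%.

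**3. Possible bias (illustration; every rate and gap is assumed)**

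Let f be the fraction of an arm excluded and k the number of points by which their mean lowest SpO2 lies below that of the retained patients. Excluding them raises the arm's mean by f × k. The bias in the difference, PEEP minus control, is

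f_PEEP × k_PEEP − f_control × k_control.

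Suppose exclusions occur in the PEEP arm only. The gaps used are 6, 12 and 18 points (0.5, 1 and 1.5 times the SD of 12), and 18 to 28 points (values of 75 down to 65 against a retained mean of 88 + 5 = 93).

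| Excluded from one arm of 72 | k = 6 | k = 12 | k = 18 | k = 23 | k = 28 |
|---|---|---|---|---|---|
| 3% (about 2 patients) | 0.18 | 0.36 | 0.54 | 0.69 | 0.84 |
| 5% (about 4 patients) | 0.30 | 0.60 | 0.90 | 1.15 | 1.40 |
| 10% (about 7 patients) | 0.60 | 1.20 | 1.80 | 2.30 | 2.80 |

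The range is 0.18 to 2.8 points, or about 4% to 56% of the 5-point design difference.

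The standard error of the difference is 12 × √(2/72) = 2.0. With no true effect, biases of 0.3, 0.6, 1.2 and 1.8 points would move the two-sided type I error from 5% to about 5.3%, 6.0%, 9.2% and 14.7%. This ignores the slight loss of sample size.

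**4. The symmetric case**

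With the same f and k in both arms, for example 5% and 12 points, the bias is 0.6 − 0.6 = 0. If f × k is larger in the control arm, the sign reverses and the bias goes against PEEP.

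**The case against.** The strongest case on the other side is that few patients will lack the primary outcome. Enrolled patients require intubation. The outcome window is short and opens only at laryngoscopy, after the allocated ventilation has done its work. A dedicated staff member records the lowest SpO2 under {18a}, and monitor memory is available for checks. Stopping the ventilation does not by itself prevent measurement. Low systolic pressure and aspiration are themselves secondary outcomes, so the plan means to count them. An imputation method is also commonly left to a statistical analysis plan, which is not shown.

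Most of this stands, and it limits what can be claimed. A reader might infer that every patient who quits or lacks data is removed, that patients whose ventilation is stopped for harm are the ones lost, and that the loss favours PEEP. The documents do not support those steps:

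- The dropout criteria say only that subjects could be dropped, and {20c} is limited to significant outcome data. A patient who quits after the lowest SpO2 is recorded is not clearly excluded.
- Section {11b} stops ventilation. It does not remove the patient from the study.
- Section {11c} speaks of hypotension from excessive lung expansion. It does not mention PEEP and is not specific to an arm.
- The stopping rule applies to both arms, and {17a} blinds the staff who ventilate and intubate. Nothing links stopping for hypotension to a lower SpO2.

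The objection does not remove the contradiction. Exclusion is stated as the rule in the section on missing data, so it is not a detail left to another document.

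**Conclusion.** The concern holds in a limited form. With high confidence, the declared intention-to-treat analysis conflicts with the exclusion rule in {20c} and the open-ended dropout criteria, and as written the result is a complete-case analysis that removes whole subjects, possibly from the complication counts too.

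Bias is a possibility, conditional on missingness being related to both arm and prognosis. Stopping under {11b} is one route by which that could happen, not one the text establishes. Neither direction nor size can be derived from the documents. The 0.2 to 2.8 points rests on assumed exclusion rates of 3–10%, assumed gaps of 6–28 points and no exclusions in the other arm.

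This should be fixed. The wording is contradictory and cheap to correct, but nothing shows that the primary result would be materially distorted.

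**What to change.** Reconcile the Dropout criteria, {11b}, {20a} and {20c}. Replace the exclusion sentence in {20c} with text to this effect:

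- All randomised patients are analysed in their assigned arm for every outcome they have recorded. A missing lowest SpO2 does not remove a patient from the complication counts.
- Stopping the allocated ventilation is not a dropout for the analysis. Outcome recording continues to the end of the window defined in {12}.
- Removal is limited to withdrawal of consent for the use of data. The Dropout criteria are shortened to match, which makes the undefined thresholds unnecessary.
- A missing lowest SpO2 is first sought in the monitor memory already mentioned in {18b}.
- For values still missing, counts and reasons are reported by arm, and a sensitivity analysis varies the missing values in both arms. One option is multiple imputation using arm and pre-intubation SpO2, with best- and worst-case bounds. A worst case applied to the PEEP arm alone would prejudge the direction. The details may sit in the statistical analysis plan.

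The cost is a few sentences of wording and a small amount of analysis. SpO2 before intubation is already collected under {18a}, so no new data are needed.
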